## BACKGROUND

2

A systematic review of 27 studies involving approximately 500,000 patients with type 2 diabetes reported that medication non‐adherence with oral medication alone or in combination with injectable insulin ranged from 6.9% to 61.5% (Krass et al., 2015). An earlier systematic review of 17 studies involving more than 900,000 patients with type 1 and 2 diabetes observed that non‐adherence to insulin therapy ranged from 14% to 57% (Davies et al., 2013). The considerable variation in non‐adherence rates reported in these reviews is likely due to methodological problems in measuring patient adherence to treatment.

Poor adherence to medication is an important and often overlooked barrier to optimizing health outcomes in patients with diabetes (Sokol et al., 2005) and is an important clinical issue for nurses working with this group of patients. For people with type 2 diabetes treatment, adherence is not limited to medication but also includes adopting and complying with lifestyle changes (e.g. eating a healthy diet, taking regular exercise and self‐blood glucose monitoring).

Polonsky (2016) reported that the most common modifiable factors affecting medication adherence in people with type 2 diabetes were perceived treatment efficacy, hypoglycaemia, treatment complexity and convenience, cost of treatment, medication beliefs and physician trust. Polonsky (2016) also concluded that no specific intervention has consistently been shown to be effective at improving adherence and recommended that a new approach to enhancing adherence be developed to target both treatment‐related burden and beliefs about treatment (Polonsky & Henry, 2016).

A number of different adherence interventions have been tested in patients with type 2 diabetes including patient education, consultation and simplifying treatment regimes. A Cochrane systematic review of adherence interventions in type 2 diabetes included 21 randomized controlled trials involving 4,135 patients. The authors reported that most of the studies were of methodologically poor quality and it was not possible to conclude which intervention characteristics constituted an effective medication adherence intervention (Vermeire et al., 2005).

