#### Patient's adherence

To determine patient adherence, we will use the Medication Adherence Reporting Scale (MARS‐5) that was initially developed and validated by (A. H. Y. Chan et al., 2020). The questionnaire has five Likert scale items, for each item answer categories ranging from 1 least adherent to 5 most adherent. The MARS scale was translated and validated in Arabic (Alsous et al., 2017) and has been used to determine adherence in patients with diabetes (Borgsteede et al., 2011; de Vries et al., 2014).

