#### Recruitment

4.10.3

Recruitment of participants will be undertaken at the outpatient clinic of the National Guard Hospital. Approximately 100 patients with type 2 diabetes are seen each week. We estimate that approximately 50% of patients will be non‐adherent according to our definition (i.e. MARS score ≥ 5). In previous adherence studies, around six patients need to be asked to get one to consent (Chien et al., 2015). This means that we can realistically expect to recruit around four patients per week to the trial. Recruitment can be expected to be completed within 5 weeks. Our recruitment will follow the following process:

Step one (checking eligibility): the treating team working in the diabetes clinic will have access to a list of patients who will be seen in the clinic each day. They will undertake an initial screen (i.e. determine they are over 18 years of age and have a diagnosis of type 2 diabetes).Step two (consent to approach): a member of the treating team will then ask patients if they would be interested in taking part in a research project about adherence to diabetes treatment (consent to approach). If they say yes, they will be given a patient information sheet and ask the patient to complete the MARS. At this time, patients will also be told that only patients who regularly miss their medication will be included in the study. Patients who score below seven on the MARS will be informed they meet inclusion criteria and be asked to provide consent. Adherent patients (i.e. those with a MARS score above eight) will be informed that “because adherence does not seem to be a problem for them, they may not benefit from the intervention and on this occasion cannot be included.” Information about the number of people who receive study information and who consent to be approached will be recorded.Step three (informed consent): from patients that meet study inclusion criteria, we will seek online informed consent. FA will explain study procedures and answer any questions participants may have. Participants will have 48 hr to consider taking part in the study at which point online informed consent will be obtained.

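### Patients screened out on one MARS self-report get a hedged reassurance about their own adherence that the score does not support; a neutral eligibility notice would avoid it (minor)

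*Protocol article*

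**What the plan says.** Section 4.10.3 (Recruitment) sets out the sequence. After an initial screen on age and diagnosis, "a member of the treating team will then ask patients if they would be interested" in a project about adherence. Those who say yes get an information sheet, and the team member will "ask the patient to complete the MARS". The section adds: "At this time, patients will also be told that only patients who regularly miss their medication will be included in the study".

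Two outcomes follow. Scores below seven lead to consent. For the others, the text reads "Adherent patients (i.e. those with a MARS score above eight) will be informed that" and then "because adherence does not seem to be a problem for them, they may not benefit from the intervention", adding that on this occasion they cannot be included. No second measure of adherence enters the decision.

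Section 4.10 (List of measures, Patient's adherence) describes the scale: "The questionnaire has five Likert scale items", with "answer categories ranging from 1 least adherent to 5 most adherent". It says that the Arabic version has been validated and that the scale has been used in diabetes. It gives no threshold and no accuracy figures.

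**The concern.** A trial must tell people why they are not enrolled, but it need not comment on their behaviour to do so. This script turns an entry rule into a remark about the patient's own medication taking, on the strength of one questionnaire. Section 2 (Background) treats poor adherence as a problem that often goes unnoticed. A non-adherent patient who hears the remark during a clinic recruitment step could take it as a reason not to raise the subject. What is at stake is an avoidable, modest risk to people whom the trial does not enrol. The feasibility outcomes in section 4.9.1 do not depend on the script.

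**Working it through.** The plan states no figure to reproduce here, so the check sets the message against the scale and its cut-offs.

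**Inputs**
- Number of items: 5, each scored 1 to 5, higher meaning more adherent (section 4.10).
- Score that triggers the message: above eight (section 4.10.3, step two).
- Score that leads to inclusion: below seven (section 4.10.3, step two).
- Inclusion criterion: below 5 (section 4.7.1).
- Definition of non-adherence in the recruitment estimate: 5 or more, with about 50% of clinic patients meeting it (section 4.10.3).

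**Step 1: range of the score.** The article does not say whether items are summed or averaged. An average cannot exceed 5, so a score above eight would never occur and nobody would hear the message. The rule works only on a total, which runs from 5 × 1 = 5 to 5 × 5 = 25 and has 25 − 5 + 1 = 21 possible values.

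**Step 2: where the message starts.** The first total above eight is 9. The item mean is 9/5 = 1.8 on a 1 to 5 scale. The position on the range is (9 − 5)/(25 − 5) = 4/20 = 20% of the way up from the least adherent end.

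**Step 3: how much of the scale it covers.**

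| Rule | Totals covered | Count of 21 |
|---|---|---|
| Below 5 (section 4.7.1) | none | 0 |
| 5 or more (recruitment estimate) | 5 to 25 | 21 |
| Below seven (step two, included) | 5, 6 | 2 |
| Neither outcome given | 7, 8 | 2 |
| Above eight (step two, message) | 9 to 25 | 17 |

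These are counts of possible totals, not shares of patients, because the article gives no distribution of scores.

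**Step 4: what remains with a sound cut-off.** Among 100 patients who complete the MARS, with prevalence *p* of non-adherence, those missed and given the message number 100 × *p* × (1 − sensitivity). Take *p* = 0.50 from the protocol's estimate, assuming that completers resemble clinic patients. Sensitivity, and a specificity of 0.90, are assumed because the documents give neither. Adherent patients given the message are then 50 × 0.90 = 45.

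| Assumed sensitivity | Non-adherent patients given the message | Share of all given it |
|---|---|---|
| 0.90 | 50 × 0.10 = 5 | 5/50 = 10% |
| 0.70 | 50 × 0.30 = 15 | 15/60 = 25% |
| 0.50 | 50 × 0.50 = 25 | 25/70 = 36% |

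The table illustrates direction only: the count is zero only at perfect sensitivity. It does not estimate what would happen in this clinic.

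**The case against.** The case on the other side is substantial, and much of it stands.

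- **The wording is hedged.** It speaks of what seems to be so and what may follow, and limits the refusal to this occasion. A reader might infer that patients are told outright that they have no adherence problem; the script does not say that.
- **The setting is not described.** A reader might picture the questionnaire filled in under the eyes of the treating team. The article does not say where it is completed or who is present, and the treating team as speaker is implied by the step rather than stated.
- **Unwilling patients are not the issue.** A reader might suppose that people who do not want to join could score themselves out. Only those who have already expressed interest complete the MARS. Being told who can join could push answers in either direction.
- **The Background remark has a narrower target.** The phrase "likely due to methodological problems in measuring patient adherence to treatment" explains variation between published studies. It says nothing about the MARS as an individual screen.
- **No absolute claim about self-report is available.** It is tempting to say that no cut-off on a self-report could ever support the message. The documents do not establish that, and they describe the MARS as validated.
- **Much of the force comes from the cut-off.** The total of 9 is a symptom of conflicting MARS thresholds, which is a separate point. With a sensible threshold, a hedged remark to high scorers is much less troubling.
- **Usual care continues.** Section 4.6 has clinicians reviewing these patients and their treatment, and nothing in the trial removes that.

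Two things survive. As the protocol stands, the script reaches patients near the least adherent end of the scale. After repair, the eligibility notice would still carry a comment on adherence that it does not need, given to whomever the screen misses.

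**Conclusion.** The point holds as a minor one. With summed items, the hedged message starts at a total of 9 (item mean 1.8) and covers 17 of 21 possible totals, so clearly non-adherent patients would receive it if the text were followed. This rests on the scoring direction in section 4.10 and on summing, the reading on which a score above eight is attainable.

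Once sections 4.7.1, 4.10 and 4.10.3 agree on the MARS, the problem shrinks to the non-adherent patients the screen misses. Their number cannot be derived from the documents. A reader might take a figure such as 5 to 15 per 100 from the illustration, but it rests on assumed accuracy and applies only to interested patients who complete the MARS, not to everyone seen in clinic.

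**What to change.** Replace the script in step two with a neutral notice. For example: the patient does not meet the entry criteria of this study, and this is not an assessment of how they take their treatment. Make no statement about the patient's adherence or likely benefit. Use the same notice for everyone who does not qualify on the MARS, so that it stays valid whatever threshold results from reconciling the sections.

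The cost is one sentence and the formal amendment through both ethics committees that section 4.13.1 requires. It can go in with the amendment that reconciles the MARS cut-offs. Data and analysis are unaffected.

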#### Allocation

4.10.4

To ensure allocation sequence is random and concealed, we will use an external randomization service (www.sealedenvelope.com
) for this trial. Sealed Envelope uses a computer‐generated random sequence and randomly permuted blocks of four, six or eight (Sealed Envelope Ltd., 2019). Allocation will be on a 1:1 ratio (adherence therapy or treatment as usual).

#### Blinding

4.10.5

This is an open‐label study. Both the participants and the researcher will be aware of group allocation. Because this is a feasibility trial, the risk of bias that this may introduce is not of particular concern.

### Data collection methods

4.11

#### Feasibility outcomes for this trial are the number of participants

In addition to the feasibly outcomes, we will record the following in the adherence therapy group:

Total duration (in minutes) of treatment.Length of each session (in minutes).Number of sessions (defined as at least a ten‐minute discussion) attended.Number of sessions cancelled.Number of sessions rescheduled.

#### Qualitative interviews

All participants will be invited to participate in follow‐up interviews after completing the weeks 12–14 follow‐up assessment. Participants from both groups will be asked about their views of being in the trial. Additionally, participants in the intervention group will be asked about the usefulness of adherence therapy, the mode of delivery and satisfaction with the experimental intervention.

### Data management

4.12

#### Data forms and security

REDCap will be adopted as an electronic Case Record Form (eCRF). REDCap was specifically designed as a secure internet‐based eCRF and has been programmed so that participants cannot make errors in data entry. For example, participants will only be able to enter age as a two‐digit numerical field. If the participant tried entering their age as 200—by adding an additional 0—they would not be able to do so. Conversely, if they entered their age as 2—by missing a 0—this would also be rejected, and the participant would be asked to enter a valid age. Participants will need to complete every field and will not be able to proceed from one question to the next unless they do so. That said, it is ethically important that participants have the option to not answer questions (eg, about gender) should they choose. Participants will be sent a link—by both SMS and email—explaining that they need to complete the study questionnaires online. They will also be informed that if they require assistance in completing the questionnaire, they can telephone the study researcher who will assist them.

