### Objectives

4.5

In this trial, we aim to establish whether patients:

Can be recruited to the trial.Complete treatment (at least five out of eight sessions) with telephone‐delivered adherence therapy.Complete study measures using an online web‐based data entry system (RedCAP).

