#### Primary outcome (feasibility)

4.9.1

The primary outcome of this trial is the feasibility of recruiting people diagnosed with type 2 diabetes to adherence therapy trial in a Middle Eastern context. Our feasibility outcomes are, therefore, the number of patients:

Asked about the study who express an interest in participating and request further information.That need to be asked to get one to provide informed consent.That complete baseline measures.Who complete treatment (defined as attending five of eight sessions with a session being defined as talking on the phone for at least ten minutes).Who complete postintervention measures.

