#### Secondary outcomes (planned outcome measures for the trial)

4.9.2

We will summarize quantitative data using descriptive statistics (mean, standard deviation, 95% CI) outcome measures. They are as follows:

Adherence determined using the MARS.Self‐reported HbA1c.Beliefs about medication, determined using the BMQ.The frequency of missing items across all the measures.

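### Forced entry in the online forms largely removes the item missingness that the trial lists as a secondary outcome, and it conflicts with the stated right not to answer

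*Protocol article*

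**What the plan says.** Three statements in the protocol article bear on each other.

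- **The entry rule** (section 4.12, Data forms and security): "Participants will need to complete every field and will not be able to proceed from one question to the next unless they do so".
- **The exception**, in the sentence that follows: "it is ethically important that participants have the option to not answer questions (eg, about gender) should they choose". The article does not describe how this works or which items it covers. Gender is given only as an example.
- **The outcome** (section 4.9.2, Secondary outcomes): "The frequency of missing items across all the measures". It stands in the same list as MARS, BMQ and self-reported HbA1c.

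Two further places matter for the secondary point about assistance. The third aim in section 4.5 (Objectives) is to find out whether patients complete the measures in the online system. Section 4.9.1 turns this into two of its counts, patients "That complete baseline measures" and patients "Who complete postintervention measures". Data forms and security also tells participants who need help with the questionnaire that "they can telephone the study researcher who will assist them".

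**The concern.** A feasibility trial counts missing items to learn whether patients can and will answer the instruments planned for the main trial. A form that refuses to move on without an entry prevents the event being counted. The figure then describes the software setting more than the patients, and a low value could be carried into main-trial planning as evidence that MARS, BMQ and the HbA1c question are acceptable.

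HbA1c shows the problem most clearly, because it is self-reported and some patients may not know their value. If that item has no way to decline, such a patient can only guess or stop. The checks described in Data forms and security reject impossible values; they cannot detect a plausible guess.

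The exception might rescue the outcome, but as worded it contradicts the rule it follows. It also leaves open whether a declined item is a missing item. Two analysts working from this text could report different frequencies from the same data.

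**Working it through.** The article gives no figure for item missingness, so there is none to reproduce. The check is to follow each reading of the text to its consequence.

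**Inputs.** 40 patients (section 4.10.2, Sample size). Five MARS items (section 4.10, Patient's adherence). The entry rule, exception and outcome as quoted above. The article does not give the number of BMQ items, so MARS serves as the worked case.

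**Items due.** If all 40 randomised patients are due one follow-up assessment, MARS responses due = 40 × 5 = 200.

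**Step 1: the entry rule alone.** Questions are answered in sequence and none can be passed over. If a patient's last answered question is number s, every item up to s is present and every later item is absent. Isolated skips number 0. The only possible missing items are those after the point where a patient abandons the form. Under this rule, item missingness is another view of form abandonment, which the two completion counts in section 4.9.1 already capture. It says nothing separate about any one instrument, and it depends on where the instrument sits in the form.

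**Step 2: add the exception.** Declined items can then run from 0 up to the number of responses due on items that carry the option.

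| Reading | MARS items countable as missing, of 200 due |
|---|---|
| Option does not cover MARS; only finished forms counted | 0 |
| Option does not cover MARS; partial forms counted | unreached items only, 0 to 200 |
| Option covers MARS; declined counts as missing | 0 to 200 |
| Option covers MARS; declined is stored as a valid response | same as row 1 or 2 |

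The article does not choose between these rows. In the first, the outcome carries no information. In the second and fourth, at most it repeats the completion counts. Only the third measures what the outcome is for.

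**Step 3: assistance.** Let C be the reported number of completers and k the number who were helped by telephone. Unassisted completers = C − k. The article gives no value for k; the possible range is 0 to 40. Section 4.9.1 reports C with no split.

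**The case against.** The strongest reply is that the exception opens with a qualifying phrase and so modifies the rule: a participant must act on each field, but the act may be to decline. On that reading declined items can be counted and the outcome works. Abandoned forms also leave items unanswered, and section 4.9.2 does not restrict the count to submitted forms. A reader might infer that item missingness is zero by construction, or that patients are forced to invent answers. The documents support neither. Zero follows only if the exception is ignored and only finished forms are counted. Invented answers require that no decline option exists on the item concerned, and the article does not say that.

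A reader might also infer that telephone help conceals whether patients can use the online system. That is not supported either. Help is given on request, the article does not say it goes unlogged, and the objective does not ask for unaided completion. If the main trial offers the same help, completion with support available is a relevant figure.

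The article also looks at online use elsewhere. Part one checks in four patients whether an online questionnaire suits this group, and the interviews in both arms cover trial procedures. This evidence is qualitative and gives neither an item-missingness rate nor an unassisted completion count.

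Item-level form settings are often left to a full protocol, and their absence here would be no finding. But the article states the rule, the exception and the outcome, and as stated they do not fit together. That part stands.

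**Conclusion.** The point holds in a limited form. Forced entry removes skipped items, so a low frequency of missing items would largely reflect the form settings. The rule and the exception conflict, and the scope of the exception and the status of declined and unreached items are undefined. Depending on the reading, the MARS contribution at follow-up is fixed at 0 of 200, limited to unreached items, or free to range from 0 to 200. No more precise size can be given without the form specification.

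This rests on the entry rule being applied to the outcome measures as written. If the full protocol already provides a decline option on every outcome item and counts its use as missing, the problem reduces to correcting the wording.

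One descriptive secondary outcome is affected. The counts of interest, consent and treatment completion in section 4.9.1 do not depend on it. The split by assistance is a useful addition to the third objective, not an error in it. The change should be made before the forms go live, because skips that the form prevented cannot be recovered afterwards.

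**What to change.** 1. Reconcile Data forms and security with section 4.9.2. Give every MARS, BMQ and HbA1c item a 'prefer not to answer / don't know' option, or replace forced entry on these items with a soft prompt that allows the participant to continue.
2. Save partial forms.
3. Define the outcome: item missingness = (blank + declined + not reached) ÷ items due. Report it by measure and assessment, with the three components shown separately.
4. State whether a form containing declined items counts as completed in section 4.9.1.
5. As a minor addition, put an 'assisted by researcher (yes/no)' field on each form and report the third objective as completed unassisted, completed assisted and not completed.

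The cost is a REDCap setting, one extra field and one table row. The downside is a few real missing values in MARS and BMQ totals, which the analysis must then handle. In a feasibility trial those values are part of what is being measured.
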